**Fig. 2 Fig2:**
[figure not shown]
Overview of load carriage exercise testing protocol. ^a^Procollagen type 1 N-terminal propeptide, bone-specific alkaline phosphatase, beta carboxy-terminal cross-linking telopeptide of type 1 collagen, albumin-adjusted calcium, ionized calcium, ^44^Ca:^42^Ca, phosphate, intact parathyroid hormone, 25-hydroxyvitamin D, 1,25-dihydroxyvitamin D, 24,25-dihydroxyvitamin D, luteinising hormone, follicle stimulating hormone, oestradiol, testosterone, and sex hormone binding globulin will be measured before load carriage. ^b^Procollagen type 1 N-terminal propeptide, beta carboxy-terminal cross-linking telopeptide of type 1 collagen, ionized calcium, albumin-adjusted calcium, phosphate, intact parathyroid hormone, sclerostin and osteocalcin will be measured at 0 and 120 min during load carriage, then 30 and 90 min after load carriage. ^44^Ca:^42^Ca will be measured at 120 min during load carriage. ^c^Procollagen type 1 N-terminal propeptide, beta carboxy-terminal cross-linking telopeptide of type 1 collagen, ionized calcium, albumin-adjusted calcium, phosphate, and intact parathyroid hormone will be measured at 20, 40, 60, 80 and 100 min during load carriage, and 15 and 60 min after load carriage.

### Data analyses

Data management will be conducted by the investigators. All data will be pseudo anonymised, and double data entry and value range checks will be performed. The investigators will collect and assess the outcome measurements. Exercise energy expenditure measured with raw accelerometery data [33] during periods of purposeful exercise, and recorded in the exercise diary, will be processed with the GENEAread R package from CRAN [39] using a cusomized, openly available script [33, 40]. The ratio of ^44^Ca to ^42^Ca (^44^Ca:^42^Ca) in urine, blood and sweat will be measured following published standard procedures [24, 25]. The calcium isotopic composition is reported as δ^44/42^Ca in parts per thousand (‰):

$$\begin{array}{l}{\delta ^{44/42}}Ca{\rm{ }}\left( {{\% _0}} \right){\rm{ }} = {\rm{ }}\\\left[ {{{\left( {^{44}Ca{/^{42}}Ca} \right)}_{Sample}}/{{\left( {^{44}Ca{/^{42}}Ca} \right)}_{Reference}}} \right]{\rm{ - }}1\end{array}$$

Change between pre- and post-load carriage urine samples will be calculated for each load carriage session.

### Statistical analyses

No previous studies have been published investigating calcium balance through natural calcium isotope ratios in response to exercise or calcium supplementation, therefore the required sample size for this study is calculated based upon data from high and low calcium diets to reflect the Control (no calcium) and Supplement (1000 mg calcium) conditions within this study. The required sample size was calculated in R (version 4.1.1) using the *‘pwr’* package based on testing the null hypothesis that there will be no difference in calcium balance between Control and Supplement conditions. Based on differences in calcium balance between women on a high (~ 1500 mg·d^− 1^) and low (~ 300 mg·d^− 1^) calcium diet (108.6 ± 127.9 vs. − 95.2 ± 24.6 mg·d^− 1^, d = 2.21) [28], and men on a low (376 mg·d^− 1^) and moderate (857 mg·d^− 1^) calcium diet (10.0 ± 6.0 vs. 0.1 ± 1.8 parts per ten thousand, d = 2.24) [22], it is anticipated that 5 people per group will be required to detect a difference in calcium balance between the Control group and Supplement group with an α of 0.05 and a 1 – ß of 0.90. The data from these trials were using chronic diets rather than acute supplementation and so we anticipate that the effect we will see will be much smaller. Therefore, a second sample size calculation was performed from PTH concentration (a secondary outcome) in response to exercise. Based on a 18.86 to 26.83 pg·mL^− 1^ [41–43] higher serum PTH during exercise without calcium supplementation compared with calcium supplementation (following a calcium meal [1352 ± 53 vs. 46 ± 7 mg [42]] or calcium drink [1000 mg·L^− 1^ [41]; 486 mg·L^− 1^ [43]), it is anticipated that 26 people will be required to detect a difference in serum PTH concentration (d = 0.667) between the Control group and Supplement group with an α of 0.05 and a 1 – ß of 0.90. A total sample of 30 will allow us to detect an effect of d ≥ 0.75 with an α of 0.01 and a 1 – ß of 0.90.

A per-protocol analysis will be performed. Significance will be accepted as p < 0.05.

#### Primary outcomes

The absolute change in urine calcium balance (^44^Ca:^42^Ca) from pre- to post-load carriage will be compared between the Control condition and Supplement condition using a one-way analysis of covariance (ANCOVA) with pre-load carriage calcium balance (either as a ratio, or both the numerator and denominator) as the covariate. The minimal important difference in absolute change in urine calcium balance between the Control condition and Supplement condition is not known.

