## Methods

This study is a non-blinded randomised crossover controlled trial. Following the completion of a screening visit to confirm study eligibility (Pre-Screening; visit 1), each participant will complete a single load carriage exercise session on two separate occasions (visits 2 and 3) completed in a randomised order; one with a calcium supplement (Supplement) (1000 mg) and one without (Control) (Fig. 1). Block randomisation using a block size of 2 will be performed and there will be no allocation concealment. All laboratory testing will be completed at the Army Human Performance Laboratory based at the Royal Military Academy, Sandhurst, UK.

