### Participants

Thirty women will complete this randomised controlled crossover trial. Participants will: be aged 18 to 36 years old; have a maximal rate of oxygen uptake ($$\dot V$$O_2max_) of ≥ 35 mL·kg^−1^·min^−1^; will be eumenorrhoeic or using the combined oral contraceptive pill, an intrauterine system, or intrauterine device; be weight stable, defined as no change in self-reported body mass ≥ 5% over the previous 3 months; have a BMI between 18 and 30 kg·m^−2^, and; not be pregnant or lactating. Women will be excluded if they: have disordered eating, defined as ≥ 20 on the Eating Attitudes Test – 26 item (EAT-26); are vitamin D deficient, defined as a total 25-hydroxyvitamin D (25(OH)D) < 30 nmol·L^−1^; have a total areal BMD T-score of < − 1; are oligomenorrhoeic or amenorrhoeic (< 9 menstrual cycles in previous 12 months); self-report as currently smoke or vape or have stopped smoking within the previous three months; are taking any medication known to affect bone or calcium metabolism (*e.g.* treatment for thyroid disorders); have a history of heart, liver, or kidney disease, diabetes, or thyroid disorder; have had a stress fracture or other bone injury in the previous 12 months, or; are anaemic (haemoglobin < 12 g·dL^−1^).

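### The one-way ANCOVA named for the primary outcome has no participant term, which conflicts with the crossover design, the paired sample sizes and the secondary models; with positive within-woman correlation it loses power

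*Protocol article*

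**What the plan says.** Methods: "This study is a non-blinded randomised crossover controlled trial", and "each participant will complete a single load carriage exercise session on two separate occasions (visits 2 and 3) completed in a randomised order", once with the calcium supplement and once without. Order is allocated in small blocks: "Block randomisation using a block size of 2 will be performed". Participants: "Thirty women will complete this randomised controlled crossover trial". The primary comparison therefore rests on 60 changes, two from each woman.

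Primary outcomes: the change in urine isotope ratio is compared between conditions by a "one-way analysis of covariance (ANCOVA) with pre-load carriage calcium balance" as the covariate, entered either as the ratio or as its two components. No participant, period or sequence term is named.

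Secondary outcomes: the linear mixed models carry participant as a random effect, with the stated purpose of handling correlation within a woman, and within-exercise data are compared by paired t-tests.

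Statistical analyses gives three sizing figures: 5 per group for calcium balance (d of 2.21 and 2.24 from diet studies), 26 for PTH (d = 0.667), and "A total sample of 30 will allow us to detect an effect of d ≥ 0.75 with an α of 0.01" with power 0.90. The analysis is per protocol, at a significance level of 0.05.

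**The concern.** A one-way ANCOVA has a single factor, here condition, and independent errors. Fitted to two rows per woman, it computes its standard error as if the rows were unrelated. Adjusting for the pre-exercise value removes only the part of the between-woman variation that the baseline explains. If women also differ consistently in how their urine isotope ratio responds to the march, their two adjusted changes are positively correlated. The model then leaves in the residual the variation that a crossover is meant to remove.

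This is more than detail left to an analysis plan. The article names a specific model for its primary outcome, and in the next section it specifies within-person structure for the other outcomes. At stake is the precision of the main result. The protocol says that the minimal important difference is unknown, so readers will rely on the interval. It also expects an effect much smaller than in the diet studies, so power lost for no reason matters.

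**Working it through.** **1. Reproduce the plan's sample sizes** (exact noncentral-t power, two-sided unless stated).

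The diet-study effect sizes check: (108.6 + 95.2)/√[(127.9² + 24.6²)/2] = 2.21, and (10.0 − 0.1)/√[(6.0² + 1.8²)/2] = 2.24.

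| Plan's figure | Paired | Two-sample |
|---|---|---|
| 5 per group, d = 2.21, α 0.05, power 0.90 | 5 (power 0.951) | 6 per group (5 gives 0.863) |
| 26, d = 0.667, α 0.05, power 0.90 | 26 (power 0.905) | 49 per group |
| N = 30, d ≥ 0.75, α 0.01, power 0.90 | power 0.902; detectable d 0.748 | power 0.60 with 30 per group |

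One-sided variants do not rescue a two-sample reading. A one-sided two-sample test gives 5 per group for d = 2.21, but 40 per group for d = 0.667. Only the paired two-sided test returns all three figures.

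**2. What the named model does to the standard error.** Let σ be the SD of a baseline-adjusted change, ρ the correlation between a woman's two adjusted changes, and n = 30.

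- True SE of the condition difference: σ√[2(1 − ρ)/n].
- SE from the one-way ANCOVA: about σ√(2/n).
- Ratio: 1/√(1 − ρ), which is 1.00, 1.20, 1.41 and 1.83 at ρ = 0, 0.3, 0.5 and 0.7.

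**3. Type I error and power, by approximation.** Let c = 2.00 be the two-sided 5% t critical value on 58 df. The test rejects when the correctly standardised difference exceeds c/√(1 − ρ). For a paired effect dz = 0.667, dz√n = 0.667 × 5.477 = 3.65, so power is Φ(3.65 − c/√(1 − ρ)).

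- ρ = 0: threshold 2.00; type I 0.045; power Φ(1.65) = 0.95.
- ρ = 0.3: threshold 2.39; type I 0.017; power Φ(1.26) = 0.90.
- ρ = 0.5: threshold 2.83; type I 0.005; power Φ(0.82) = 0.79.
- ρ = 0.7: threshold 3.65; type I 0.0003; power Φ(0.00) = 0.50.

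**4. Simulation.** Thirty women, balanced sequences, no period effect, correlation 0.5 between baselines and a baseline slope of −0.5 (both assumed). The one-way ANCOVA on 60 rows (57 df) is set against a regression of within-woman differences on baseline difference and period (27 df).

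| ρ (assumed) | ANCOVA type I | ANCOVA coverage of 95% CI | ANCOVA power | ANCOVA CI width relative to paired |
|---|---|---|---|---|
| 0 | 0.050 | 0.950 | 0.95 | 0.97 |
| 0.3 | 0.020 | 0.980 | 0.89 | 1.15 |
| 0.5 | 0.006–0.007 | 0.994 | 0.79 | 1.36 |
| 0.7 | 0.001 | 0.999 | 0.50–0.51 | 1.76 |

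Ranges show two separate runs. The paired model holds type I error near 0.05, coverage near 0.95 and power at 0.93 to 0.94 throughout. The simulated width ratios are a little below 1/√(1 − ρ) because the paired model has fewer degrees of freedom.

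**5. Period.** Blocks of 2 give 15 women per order, so a period effect cancels from the condition estimate and only inflates the residual. A period shift of 0.5 SD lowers ANCOVA power from 0.79 to 0.75 at ρ = 0.5, and from 0.51 to 0.47 at ρ = 0.7. It leaves the period-adjusted paired model unchanged.

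**The case against.** The strongest reply is that the article is condensed. It calls the trial a crossover, speaks of conditions, sizes on a paired basis and uses paired tests elsewhere. One-way may mean only that there is one factor, with a repeated-measures qualifier lost in editing. This is possible, and the protocol nowhere says that the 60 values come from 60 women. But the model as printed has no participant term, and the neighbouring section shows that the authors state one where they intend it. The wording needs correcting under either reading.

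Second, the relevant correlation may be low. Taking the pre-to-post change already removes a woman's stable isotope level, the covariate removes more, and assay noise remains (2-SD reproducibility 0.06‰). This stands: nothing in the protocol supports 0.5 or 0.7 over 0 or 0.3.

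Third, the 26 and the 0.667 belong to PTH, a secondary outcome whose mixed model does include participant, and the d ≥ 0.75 is not tied to a named outcome. This also stands. The power figures above illustrate the loss and do not forecast power for the isotope outcome. Only the 5 per group was calculated for calcium balance, and it too is a paired figure. Holding the paired effect fixed also means that the raw effect shrinks as ρ rises, which is part of why the power column falls so steeply.

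A reader might infer that the trial needs 49 women per condition. That does not follow: it puts a paired effect into a two-sample formula, and the two scales agree only at ρ = 0.5. With the paired effect held at 0.667, an unpaired comparison needs about 25 per condition at ρ = 0, 35 at 0.3, 49 at 0.5 and 80 at 0.7.

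**Conclusion.** The inconsistency is real and sits in the only analysis stated for the primary outcome. The named model does not match the design, the sizing or the secondary models, and its standard error is right only if a woman's two adjusted changes are uncorrelated.

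The size of the harm depends on a correlation that the protocol does not give: none at 0, modest at 0.3 (power 0.89 against about 0.94), and serious at 0.5 to 0.7 (0.79 to 0.50). These figures assume 30 women with complete data, a paired effect of 0.667 and two-sided α of 0.05.

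Two stronger readings are not supported. A reader might infer that the primary p-value and interval will simply be wrong or will produce false positives. With positive correlation they err on the cautious side; inflation would need a negative correlation, for which the protocol gives no reason. A reader might also infer that omitting period biases the estimate. Sequences are balanced at randomisation, so bias arises only if per-protocol exclusions leave the two orders unequal. Period is the lesser point.

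**What to change.** In Primary outcomes, replace the one-way ANCOVA with one of these within-woman analyses:

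- Regress each woman's Supplement-minus-Control change on her difference in pre-exercise values and on period.
- Fit a linear mixed model of the change with condition and period as fixed effects and participant as a random effect. Split the pre-exercise value into the woman's mean over her two sessions and each session's deviation from it.

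The split matters. An unsplit session baseline blends the between-woman and within-woman slopes, so that model is not equivalent to the difference regression.

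Then state the detectable paired effect for the primary outcome under the chosen model. As a guide, a plain paired t-test with 30 women detects 0.61 at α 0.05 and 0.75 at α 0.01, each with power 0.90. Adjusting for baseline difference and period leaves 27 rather than 29 degrees of freedom.

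The cost is wording, plus one or two degrees of freedom. No new data or visits are needed, and the change should be made before the outcome data are analysed.

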#### Secondary outcomes

Circulating measures of calcium and bone metabolism during load carriage will be compared between Control and Supplement conditions, and changes in knee flexor and extensor strength will be compared between pre- and post-load carriage, using linear mixed models with the restricted maximum likelihood estimation to allow incorporation of incomplete data. Time and group (Control or Supplement) will be assigned as fixed effects and participant will be assigned as random effects to account for within participant correlation for repeated measures. Within exercise data will be compared between trials using paired sample *t*-tests.

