This study will investigate the effect of calcium supplementation on calcium and bone metabolism in response to load carriage exercise (standard military fitness test; 2 h, 20 kg, 6.4 km·h^− 1^) in military women, a population at increased risk of stress fracture during military training compared with men [3]. It is hypothesised that calcium supplementation will attenuate the decline in serum ionized calcium and increase in PTH and bone resorption, and prevent a negative calcium balance during load carriage. A secondary aim will investigate the effect of load carriage on quadricep and hamstring strength. It is hypothesised that quadricep and hamstring strength will be lower following load carriage.

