In the 24 h preceding each load carriage session participants will be rested (no exhaustive exercise) and will not apply skin moisturizer. Participants will arrive at the laboratory after an overnight fast, have an indwelling cannula inserted in a vein in the antecubital fossa, and a resting blood sample taken (Fig. 2). A calcium supplement (2 × 500 mg; Calcichew) will be given to each participant completing the Supplement condition ~ 60 min before starting the load carriage exercise [8]. Sweat collectors (Macroduct Sweat Collector, ELITech Group, France) [35] will be attached to the forearm for the measurement of sweat calcium excretion during exericse. A 120 min session of load carriage exercise will be completed. The load carriage exercise is a fitness test completed by the infantry. Participants will walk 12.8 km on the treadmill at 6.4 km·h^− 1^ for 120 min whilst wearing a 20 kg military backpack. Expired gases, heart rate, and rating of perceived exertion will be measured throughout the exercise. The first urine void upon waking (Fig. 2), and a urine void within ~ 1 h of the cessation of load carriage, will be obtained for the measurement of calcium isotopes for the calculation of bone calcium balance. Nude body mass will be measured before and immediately after exercise for the determination of sweat loss and calculation of sweat calcium excretion; post-exercise body mass will be adjusted for water consumed *ad libitum* during exercise. Calcium concentration of water consumed during exercise will be recorded. Blood samples will be taken at 0 min, and then every 20 min during, and 15, 30, 60, and 90 min following, load carriage. Blood samples fractioned into serum and plasma will be analysed for markers of bone formation, bone resorption, and calcium metabolism. Whole blood will be analysed immediately for blood lactate concentration (Lactate Pro 2, Arkray, Japan), ionized calcium, haemoglobin and haematocrit (i-STAT Alinity, Abbott, USA; CHEM8^+^, Abbott, USA) (Fig. 2). Isokinetic (60°·s^− 1^ and 180°·s^− 1^) and isometric (90° knee flexion) maximal voluntary contraction of the knee extensors and flexors (System 4, Biodex Medical Systems, USA) will be measured before and immediately after load carriage exercise. Researchers will monitor the laboratory testing procedures to ensure adhereance to study protocols; there is no criteria for the study to be discontinued.

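### The serial blood-marker analysis gives the pre-supplement resting sample no stated baseline role, although the 0 min sample is already post-dose in the Supplement session

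*Protocol article*

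**What the plan says.** The section Load carriage 1 and 2 gives the order of events. Fasted participants "have an indwelling cannula inserted in a vein in the antecubital fossa, and a resting blood sample taken (Fig. 2"). The calcium "will be given to each participant completing the Supplement condition ~ 60 min before starting the load carriage exercise". Then: "Blood samples will be taken at 0 min, and then every 20 min during, and 15, 30, 60, and 90 min following, load carriage".

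The Fig. 2 legend lists the assays. Footnote a covers the sample whose analytes, ending with "testosterone, and sex hormone binding globulin will be measured before load carriage", include P1NP, βCTX, ionized and albumin-adjusted calcium, phosphate and iPTH. Footnote b lists the same six again, with sclerostin and osteocalcin, and says they "will be measured at 0 and 120 min during load carriage, then 30 and 90 min after load carriage". The legend thus counts 0 min as part of the exercise period.

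The Background states the hypothesis as a change: "calcium supplementation will attenuate the decline in serum ionized calcium and increase in PTH and bone resorption".

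Secondary outcomes sets the analysis: "Circulating measures of calcium and bone metabolism during load carriage will be compared between Control and Supplement conditions". It uses a REML mixed model with fixed time and group and random participant, plus paired t-tests for within-exercise data. It names no baseline covariate or reference time for the blood markers and does not list the levels of time. Primary outcomes, by contrast, adjusts the urine isotope change for its pre-exercise value.

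**The concern.** Each of the six markers has two pre-exercise values, and they are not interchangeable. The resting value is untreated in both sessions. The 0 min value is untreated in Control but about an hour post-dose in Supplement. The analysis section does not say what either is for.

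Two things are at stake.

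- **Precision.** The participant random effect removes stable differences between women. It does not remove differences between one woman's two sessions, which are at least two weeks apart and, for some contraceptive users, not tied to a cycle phase. The resting sample measures that variation before dosing.
- **Choice of reference.** The hypothesis speaks of a decline and a rise, which need a starting point. If 0 min were later chosen, whatever the supplement had already done by then would be subtracted from its effect.

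PTH is the outcome behind the second sample-size calculation, so the point bears on the variable that supports the planned 30 women.

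**Working it through.** **1. The plan's own figures.** Inputs from Statistical analyses: d = 0.667, α = 0.05, power 0.90, n = 26; and d = 0.75, α = 0.01, n = 30. For a two-sided paired t-test, power comes from the noncentral t with n − 1 degrees of freedom and noncentrality d√n.

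- d = 0.667, α = 0.05: n = 26 gives power 0.905, so 26 reproduces.
- d = 0.75, α = 0.01, n = 30: power 0.902, which also reproduces.
- d = 0.667, α = 0.05, n = 30: power 0.94.

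The PTH effect is described as a difference in concentration during exercise, so it matches a comparison of levels.

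**2. Gain from adjustment.** Take each woman's Supplement-minus-Control difference on exercise, and the same difference at rest. Let ρ be their correlation, which the documents do not give. Adjustment multiplies the variance of the on-exercise difference by 1 − ρ², and the detectable d by √(1 − ρ²). Unadjusted, the detectable d at n = 30, 90% power and two-sided 0.05 is 0.612.

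| Assumed ρ | Variance removed | Detectable d |
|---|---|---|
| 0 | 0% | 0.612 |
| 0.3 | 9% | 0.612 × 0.954 = 0.584 |
| 0.5 | 25% | 0.612 × 0.866 = 0.530 |
| 0.6 | 36% | 0.612 × 0.800 = 0.490 |

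These figures leave out the cost of estimating the slope. For a normally distributed covariate that cost inflates the variance by (n − 2)/(n − 3) = 28/27. Adjustment therefore pays only if (1 − ρ²) × 28/27 < 1, that is ρ² > 1/28, or ρ above about 0.19. With this cost and the lost degree of freedom, the detectable d is about 0.60 at ρ = 0.3 and 0.50 at ρ = 0.6.

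**3. If 0 min were used as the reference (not planned).** Let f be the share of the PTH effect already present at 0 min, an assumption, with the SD held fixed. Change from 0 min has d = 0.667 × (1 − f).

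- f = 0.25: d = 0.50, power at n = 30 is 0.75.
- f = 0.50: d = 0.33, power 0.42.

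**4. Level comparison as worded.** There are 11 samples from 0 min onwards (0 to 120 min every 20 min makes 7, plus 4 in recovery). With the full effect at the other 10 and equal weights, the group effect keeps (10 + f)/11 of its size, that is 0.91 to 1.00. Nothing is subtracted.

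**5. Resting sample as one more level of time.** With only main effects of time and group, an untreated time point joins the average and the group effect keeps (10 + f)/12, that is 0.83 to 0.92.

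**The case against.** A reader might infer that the plan measures change from 0 min and so removes part of the calcium effect. The document does not support this. Secondary outcomes compares levels between conditions and speaks of changes only for knee strength. The power figures in step 3 describe a contrast that nobody has announced.

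A reader might also infer that the resting sample is discarded. That too goes beyond the text. The levels of time are not listed, and the article uses the phrase about load carriage loosely: read literally, it would also exclude the recovery samples. The full protocol or analysis plan may settle the matter.

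Three further objections stand in part. First, in a randomised crossover a level comparison without baseline adjustment is unbiased, so leaving it out is not an error. Second, ρ, f and the constant SD are all assumed, and a paired t-test stands in for a mixed model. Third, a covariate drops sessions with a missing resting value unless this is handled, which works against the stated aim of using incomplete data.

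Fig. 2 itself is not shown, so that the resting sample precedes the dose rests on the order of the sentences.

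What the objection does not remove: the article does specify a model, that model has no baseline term although the primary analysis has one, and the pre-dose sample is already drawn and assayed.

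**Conclusion.** The point holds as one of precision and of naming the reference sample, not of bias. Six serial markers have a pre-supplement value with no stated baseline role, and the 0 min value is post-treatment in one condition only. At an assumed ρ of 0.3 to 0.6, adjustment removes 9% to 36% of the variance and lowers the detectable d from 0.61 to between 0.58 and 0.49, slightly less after the cost of estimating the slope. Below a ρ of about 0.19 there is no gain. The sample-size figures reproduce and are not undermined, since they rest on levels. The reference sample should be fixed before data are seen, because the apparent size of the attenuation depends on it.

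**What to change.** In Secondary outcomes, for each serial marker with a resting value:

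- Name the pre-supplement resting sample as the session baseline. Enter it as a covariate in two parts: the session value and the woman's mean over both sessions. This keeps the within-woman slope separate from the between-woman one.
- Treat 0 min as the first post-dose time point, and do not define a decline or rise as change from 0 min.
- State how a missing resting value is handled so that incomplete sessions are kept. One way is to model the resting value jointly as a response, with a common mean for both conditions at rest and a correlation between samples of the same session. Adding it as an ordinary level of time in a main-effects model would dilute the group effect (step 5).

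No new samples or assays are needed. The cost is wording, one or two degrees of freedom, and the missing-value rule.

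### The secondary mixed model lists only time and group, so as written it tests a mean-level difference and not whether calcium attenuates the exercise-induced change

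*Protocol article*

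**What the plan says.** The Background sets the hypothesis: "It is hypothesised that calcium supplementation will attenuate the decline in serum ionized calcium and increase in PTH and bone resorption". The Discussion again describes the aim as finding out whether the supplement dampens a disturbance caused by exercise.

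The Secondary outcomes section gives the comparison, "Circulating measures of calcium and bone metabolism during load carriage will be compared between Control and Supplement conditions", and the model, "Time and group (Control or Supplement) will be assigned as fixed effects", with participant as a random effect, fitted by restricted maximum likelihood. It names no group × time term, no time-specific contrast and no baseline adjustment for the circulating markers. A closing sentence adds: "Within exercise data will be compared between trials using paired sample" *t*-tests. It does not say which variables these tests cover.

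On sampling, the section Load carriage 1 and 2 describes a resting sample, then the supplement about 60 min before exercise, and then: "Blood samples will be taken at 0 min, and then every 20 min during, and 15, 30, 60, and 90 min following, load carriage".

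**The concern.** Attenuation means that the rise or fall from baseline is smaller under one condition than under the other. In a model for repeated samples this is a group × time effect. A model with group and time as separate terms assumes that the two time courses are parallel, so the quantity in the hypothesis is fixed at zero before any data are seen.

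Two misreadings could follow. A genuine effect late in exercise or early in recovery could be reported as small because it is averaged with samples where little happens. Conversely, a significant group term produced by a steady difference in level could be reported as attenuation. If the interaction or a time point is chosen only after the data are seen, the choice is open to the charge of being data-driven. Ionized calcium, PTH and bone resorption are all named in the hypothesis and are all affected.

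**Working it through.** **1. What the stated model can estimate.** Write the mean for condition g (0 = Control, 1 = Supplement) at time t as μ + τ(t) + γ·g. The difference between conditions in change from time s to time t is then

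[τ(t) − τ(s)] − [τ(t) − τ(s)] = 0

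for every pair of times. Attenuation has no parameter. With complete data, the estimate of γ is the plain average of the between-condition differences over the samples modelled.

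**2. Samples.** The schedule gives 0, 20, 40, 60, 80, 100 and 120 min (7) and +15, +30, +60 and +90 min (4), so 11. The resting sample makes 12. The Fig. 2 legend agrees for the main panel: 1 + 4 + 7 = 12. Rest is described before the supplement. The 0-min sample falls about 60 min after it.

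**3. The plan's own figures.** A two-sided paired t-test with d = 0.667, α = 0.05 and power 0.90 gives N = 26 (power 0.905). N = 30 with d = 0.75 and α = 0.01 gives power 0.902. Both stated figures reproduce. They rest on a single paired difference and do not depend on the mixed model.

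**4. Shrinkage of the group term.** Share of the peak effect = mean of the effect profile over the samples modelled. The profiles are assumptions, since the article gives none. Power is for N = 30, peak d = 0.667 and two-sided α = 0.05. It takes the SD of the averaged difference as √((1 + 11ρ)/12) times the single-time SD, where ρ is the assumed correlation between paired differences at different times.

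| Assumed profile | Share, 12 samples | Share, 11 (no rest) | Power of group term (12 samples), ρ = 0.2 / 0.5 / 0.8 |
|---|---|---|---|
| Full from 0 min onward | 0.917 | 1.000 | 1.000 / 0.993 / 0.947 |
| Ramp to 120 min, then held | 0.625 | 0.682 | 0.990 / 0.850 / 0.685 |
| Ramp to 120 min, decay to zero at +90 | 0.444 | 0.485 | 0.860 / 0.569 / 0.412 |
| 100, 120, +15 and +30 min only | 0.333 | 0.364 | 0.625 / 0.360 / 0.256 |
| 120 min only | 0.083 | 0.091 | 0.088 / 0.069 / 0.062 |

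For example, the third profile sums to 3.5 over 0–120 min plus 75/90 + 60/90 + 30/90 = 1.833 in recovery, and 5.333/12 = 0.444. For comparison, a paired test at 120 min alone has power 0.942. A contrast in change from rest to 120 min has effect size 0.667/√(2(1 − ρ)) and power 0.797, 0.942 and 1.000 at ρ = 0.2, 0.5 and 0.8.

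**5. Modelling 0–120 min only.** A ramp from 0 at 0 min to 1 at 120 min averages (0 + 1 + 2 + 3 + 4 + 5 + 6)/6 ÷ 7 = 0.5. The time courses are still forced to be parallel.

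**6. Simulated fits.** REML mixed models were fitted with 30 participants, 12 samples, a participant SD of 1.0, a residual SD of 0.7 and 30 replicates (absolute values shown).

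| Truth | Group term, additive model | Interaction, rest to 120 min |
|---|---|---|
| Attenuation: ramp-then-decay, peak 1.0 | about 0.45 | about 0.95 (true 1.0) |
| Constant shift of 0.44 at all 12 samples, no attenuation | about 0.43 | about 0.02 (true 0) |

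The additive group term is almost the same in the two cases. Only the interaction separates them.

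**The case against.** The strongest reply is that naming the two factors may be shorthand in a condensed article, with the cross term and contrasts set out in a fuller document. That is possible. But the article does more than stay silent: it states which effects are fixed, and nothing in it points to an interaction. A statistician following the text would fit the additive model.

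Three further replies have partial force.

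- The comparison is worded as during load carriage, so the resting and recovery samples may not be modelled. This stands against treating 12 as a settled denominator. It does not restore a test of attenuation, as step 5 shows.
- The paired *t*-tests could be comparisons at single time points. They could equally concern heart rate, expired gases and perceived exertion, which are also recorded throughout exercise. Their variables are undefined, and they are not tied to change from baseline.
- In a randomised crossover, levels before the supplement are equal in expectation, so the group term is a valid test of a supplement effect on mean level. This stands in full.

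A reader might also infer that the model dilutes any effect, or that one third to one half is the expected loss. The documents do not support this. If the effect is already full at 0 min, shrinkage is 0–8% and averaging can raise power (0.947 to 1.000, against 0.942 at 120 min alone).

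**Conclusion.** The point holds in this form: followed as written, the secondary mixed model tests a mean-level difference between conditions and cannot test the stated attenuation hypothesis. That conclusion follows from the model's form and needs no assumption about the data.

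The effect on estimates is conditional. Shrinkage ranges from 0–8% for an effect that is full from 0 min to about two thirds for one present at 4 of 12 samples, and more for a single-sample effect. These figures depend on assumed profiles, on which samples are modelled and, for power, on an assumed ρ of 0.2 to 0.8. The documents fix none of these.

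Because PTH was used to size the trial, a reader might infer that the sample size is undermined. It is not, since N = 26 and N = 30 both reproduce as paired comparisons. The primary ANCOVA is a separate analysis, and the strength hypothesis needs only the time effect, which the model has. This is a should-fix confined to the circulating secondary outcomes.

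**What to change.** In Secondary outcomes, for the circulating markers:

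- Add the group × time interaction, with time as a categorical factor.
- State which samples are modelled, and use the pre-supplement resting value from each session as the baseline. The 0-min sample should not take that role, because it is drawn about 60 min after the supplement.
- Name one contrast per key marker (ionized calcium, PTH, βCTX) in advance, for example Supplement versus Control in change from rest to 120 min. This contrast includes any shift that arises between the supplement and the start of exercise. If the interest is only in what happens during exercise, the 0-to-120-min contrast from the same model can be reported beside it.
- Say which variables the paired *t*-tests cover.

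The strength analysis can stay as it is. The cost is analysis wording and a slightly larger model, settled before the data are analysed. No further blood samples or assays are needed. Sclerostin and osteocalcin are first listed at 0 min, but neither is named in the hypothesis, so extra resting assays of them are not part of this fix.
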